#### Secondary outcomes

2.9.2

We estimated the effects of this intervention on several secondary outcomes.

The duration of URTI symptoms was verified by all random patient exit interviews via phone call follow-up after 14 days.Adverse events, severe adverse events, and adverse events related to antibiotics include allergic reactions, rashes, and pruritus.The proportion of eligible patients who received subsequent antibiotics for any reason within 14 days of follow-up was verified by all randomized patient exit interviews via telephone follow-up. Subsequent antibiotic use was defined as any antibiotic use within 14 days of follow-up, excluding initial antibiotic prescriptions.The proportion of eligible patients with URTIs who re-attended outpatient clinics or emergencies within 14 days, and whether antibiotics were prescribed, compared to intervention hospitals and controls.The proportion of eligible patients who were hospitalized within 14 days was verified by all randomized patient exit interviews via phone call follow-up after 14 days, excluding patients referring to the initial ED visit.

### Data collection and management

2.10

For every patient, quantitative and qualitative data were obtained from electronic medical records, where available, and clinical outcomes were derived from telephone follow-up evaluations. A secure web-based database was established for data collection, with access restricted to principal investigators and site co-investigators. Collected variables included consultation date, demographic characteristics (gender and age), diagnosis, prescribed medications, body temperature, and relevant laboratory results. Each participant was assigned a unique study number to ensure anonymity throughout the data entry and analysis.

All site investigators entered and modified the data using the original source-verified records. The coordinating center conducted regular data audits to verify the accuracy and protocol compliance. The identified discrepancies triggered a standardized query process for clarification and correction by the designated staff. Before study initiation, the principal investigator conducted standardized training for all co-investigators to ensure consistent data collection procedures. The database incorporates range checks and value validation to minimize data entry errors.

### Statistical analysis

2.11

This study will adhere to the CONSORT guidelines for cluster-randomized trials. Based on the intention-to-treat principle, a full analysis set (FAS) will be applied to all randomized subjects at all participating hospitals. Per-protocol analysis of the primary endpoint included only participants who underwent interventions. FAS will be used to study baseline characteristics and primary outcome comparison. A two-sided significance level of 5% will be used to determine the statistically significant results.

Pre-specified subgroup analyses for the primary endpoint will be performed as part of the primary analysis. For between-group comparisons, generalized linear models will be used, with treatment group, hospital level as fixed effects and healthcare center as a random effect. Relative risks (RRs)and risk differences with confidence intervals (CIs) will be calculated. Symptom duration will be assessed using Kaplan–Meier curves with 95% CIs. Formal comparisons between the two groups will beperformed using the Cox proportional hazards model, with the treatment group and hospital level as fixed effects and healthcare center as a Gaussian random effect (frailty). A detailed statistical analysis plan will be prepared before data lock.

#### Handling of missing data

2.11.1

For the missing primary outcome measure, we will assume that the data are missing at random (MAR) and thus “ignore” in the primary analysis. However, if > 5% of the primary outcome measures that should have been available for analysis are missing, a sensitivity analysis will be conducted in addition to a primary MAR analysis.

For missing baseline prognostic variables, the mean value calculated from the observed non-missing instances of the baseline prognostic variable will be used for the imputation. These imputed means will be calculated based on pooled data from both study groups and will notbe computed within groups using group-specific data. If imputation is required as a baseline prognostic variable, the proportion of cases with initially missing values will be reported.

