#### Eligibility criteria for participants

2.4.2

Eligible patients had to satisfy all of the following criteria: aged ≥ 18 years, had a URTI diagnosis during the baseline and intervention periods, with laboratory tests indicating white blood cells > 10 × 10^9^/L or C-reactive protein (CRP) ≥ 10.0 mg/L, and required the use of antimicrobial agents with at least one focal sign or symptom. Qualifying manifestations included (1) fever, (2) cough, (3) rhinitis (sneezing, nasal congestion, or rhinorrhea), (4) pharyngitis (sore throat), (5) dyspnea, (6) wheezing, or (7) chest pain.

Exclusions would apply to patients with other infections in addition to URTIs; patients who require hospitalization or referral to a higher-level medical institution; individuals unable to tolerate oral medications; special populations, including those with neutropenia, bone marrow suppression, active radio-chemotherapy, immunosuppression, HIV/AIDS, primary immunodeficiency, pregnancy, or severe psychiatric disorders and patients who were not prescribed antimicrobial agents during this visit.

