### Randomization

2.6

A total of 28 hospitals were eligible for the trial, comprising 9 Tier-3 Grade-A hospitals, 15 Tier-3 Grade-B hospitals, and 4 Tier-2 Grade-A hospitals, based on China’s tiered hospital classification system. Under this system, hospitals are categorized into three tiers (Tier-1 to Tier-3), with Grade-A representing the highest service quality within each tier. Randomization was performed at the hospital level. All participating institutions were stratified by hospital grades to ensure balanced cluster distribution between the study arms. Hospitals within each stratum were randomly allocated to either the intervention or control group in a 1:1 ratio, using a computer-generated sequence. To maintain allocation concealment, randomization was performed after obtaining each hospital’s consent to participate.

To minimize observer bias, randomization was conducted by a member of research team who was not involved in recruitment or participant enrolment. Due to the interventional nature, masking of researchers and participants was impossible; however, telephone follow-up personnel and trial statisticians remained blind to cluster allocation until the trial was concluded. Regular meetings were conducted among the investigators to monitor research progress and effectively address any issues in this study.

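### The imputation rule for baseline prognostic variables has nothing to act on, because the stated models adjust for no patient-level variable; measured case-mix differences therefore stay in the treatment estimate

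*Protocol article*

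**What the plan says.** Section 2.11.1 (Handling of missing data) gives a specific rule that opens with "For missing baseline prognostic variables" and continues: "the mean value calculated from the observed non-missing instances of the baseline prognostic variable will be used for the imputation". The mean is pooled over both arms, and the share of values that were missing is to be reported.

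Section 2.11 (Statistical analysis) describes the model for between-group comparisons "with treatment group, hospital level as fixed effects and healthcare center as a random effect". The Cox model for symptom duration has the same two fixed effects, with centre as a Gaussian frailty. The same section says "FAS will be used to study baseline characteristics and primary outcome comparison", announces subgroup analyses without naming their variables, and defers detail to an analysis plan to be written before data lock.

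Section 2.10 (Data collection and management) lists what is collected: "demographic characteristics (gender and age), diagnosis, prescribed medications, body temperature, and relevant laboratory results". It limits this to what the electronic records hold. Section 2.4.2 (Eligibility criteria for participants) admits patients "with laboratory tests indicating white blood cells > 10" × 10⁹/L or, as an alternative, with CRP of at least 10.0 mg/L. It excludes those given no antimicrobial at the visit. Section 2.6 (Randomization) states that "masking of researchers and participants was impossible".

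**The concern.** A rule for filling in prognostic covariates makes sense only if such covariates enter an analysis. The models, as their terms are listed, contain none. The two sections therefore describe different analyses, and a later plan must depart from one of them, either by adding covariates or by dropping the rule. If that choice is made late and without a record, it can look driven by the data.

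The design makes the choice matter. Hospitals are allocated first. Patients then enter at sites whose staff know the arm, and entry depends on a prescribing decision made by those staff. With 14 hospitals per arm, randomisation alone gives limited protection against case-mix differences. Any difference in age or severity that also bears on the choice of IV treatment would pass into the unadjusted risk difference. Case-mix differences between hospitals also add to the between-hospital variance, which limits power.

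**Working it through.** **Step 1: does the rule have a target?** The stated model terms are treatment, hospital level and centre.
- Treatment and centre are fixed by the design and cannot be missing.
- Hospital level is the randomisation stratum, and section 2.6 gives it for every hospital: 9 + 15 + 4 = 28.

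No term in either stated model can need imputing, so the rule has no target there. A descriptive baseline table does not supply one, because it can report observed values and the number missing.

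**Step 2: reproduce the plan's power.** Inputs from section 2.5 (Sample size): proportions 0.60 and 0.48, 14 clusters of 100 per arm, ICC 0.04, two-sided unpooled Z test at 0.05.
- Design effect: 1 + (100 − 1) × 0.04 = 4.96.
- Effective n per arm: 1,400 / 4.96 = 282.3.
- SE: √[(0.60 × 0.40 + 0.48 × 0.52) / 282.3] = √(0.4896 / 282.3) = 0.0416.
- Power: Φ(0.12 / 0.0416 − 1.96) = 82.2%, against the stated 82%.
- Dropout: 1,400 / 0.9 = 1,556, as stated.

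Both figures reproduce.

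**Step 3: what adjustment might gain in precision.** The documents do not say how much of the between-hospital variance the covariates explain. Assume 12.5% to 25%, so that the effective ICC is 0.04 × 0.875 = 0.035 or 0.04 × 0.75 = 0.03.

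| Effective ICC | Design effect | Effective n per arm | Power |
|---|---|---|---|
| 0.04 | 4.96 | 282.3 | 82.2% |
| 0.035 | 4.465 | 313.5 | 85.9% |
| 0.03 | 3.97 | 352.6 | 89.6% |

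If the covariates explained only variation within hospitals (5% to 30% of it) and none between hospitals, power would be 82.5% to 84.3%. The gain comes almost entirely from the between-hospital part.

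**Step 4: what imbalance might do to the estimate.** The documents give no inputs, so these are assumptions. Bias in the risk difference ≈ (difference between arms in the share of sicker patients) × (difference in IV use between sicker and other patients).
- Smallest case: 0.05 × 0.20 = 0.01.
- Largest case: 0.20 × 0.40 = 0.08.

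That is 1 to 8 percentage points, against a target difference of 12.

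**The case against.** The best reply is that this is a condensed article, that a detailed analysis plan is promised, and that covariate lists usually belong there. Section 2.11 never says that the listed terms are the only ones, and treatment, stratum and a random centre effect form a valid analysis for a stratified cluster trial. This stands in part: the stated model is not invalid, and the later plan may name covariates. It does not remove the mismatch, because the article is not silent here. It fixes an imputation rule and lists model terms, and the two do not meet.

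Four stronger readings are tempting, and the documents do not support them.
- **That the collected variables go unused.** Baseline characteristics are described in the full analysis set, laboratory values decide eligibility, and the unnamed subgroups may draw on these variables. Only their absence from adjustment in the stated models is shown.
- **That they are recorded for every patient.** Section 2.10 depends on what the records hold. Section 2.4.2 needs WBC or CRP, not both, and section 2.8 (Follow-up) rules out extra laboratory tests.
- **That CRP and WBC can safely go into the primary model with mean imputation.** They are measured after allocation, and the decision support in section 2.7.2 refers to CRP, so testing may differ by arm. A pooled mean is then a doubtful fill.
- **That adjustment would correct the imbalance.** It acts on measured factors only and cannot undo selection from admitting only patients prescribed an antimicrobial.

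Two further replies also carry weight. Imbalance is possible but not demonstrated, and the waiver of written consent closes one route to differential entry. The power gain only restates an assumed variance share.

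**Conclusion.** The point holds in a limited form. Sections 2.11 and 2.11.1 do not fit together: the imputation rule has no variable to act on in either stated model, and patient-level values that the trial collects are not used for adjustment there. Measured case-mix differences that arise after unmasked allocation would remain in the treatment estimate.

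The size is uncertain. Power of about 86–90% instead of 82% assumes that the covariates explain 12.5–25% of the between-hospital variance and that the ICC of 0.04 is unadjusted, which the article does not say. The possible bias of 1 to 8 points rests wholly on assumed imbalances. The sample size and power as stated are correct. This should be changed because it bears on the primary estimate and is easy to settle, but it does not invalidate the trial.

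**What to change.** Reconcile sections 2.11 and 2.11.1 before data lock and before the statisticians are unblinded:

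1. Name age, sex and index-visit body temperature as fixed effects in the primary model, next to treatment, hospital level and the random centre effect. The pooled-mean rule then has a defined scope.
2. Obtain the RR and risk difference by standardisation over these covariates.
3. Report the model without them as a sensitivity analysis.
4. Add CRP and WBC only in a further sensitivity analysis that gives missingness by arm.
5. State that adjustment covers measured factors only and does not address selection through the requirement for an antimicrobial prescription.

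No new data are needed. The costs are some programming for the standardisation step and a dated, reasoned record of the change to the published model. That record matters because planned inclusion ended on 31 January 2026, before the article appeared on 10 March 2026. If the data have already been locked or unblinded, the adjusted analysis should be labelled as added afterwards.

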### Ethics and dissemination

2.12

This study was reviewed and approved by the medical ethics committee of the Second Affiliated Hospital, Zhejiang University School of Medicine, China (Approval No. 2024–0799), as well as by the ethics committees of all participating centers. All study sites were approved by the local institutional ethics committee. The requirement for written informed consent from the patients was waived by the ethics committee to ensure minimal disruption to routine practice. The results of this trial will be published in peer-reviewed journals and presented at conferences.

An independent Trial Steering Committee (TSC) oversees this study. TSC, composed of clinical experts, statisticians, and independent advisors, monitors the trial progress, evaluates protocol adherence, addresses significant deviations, and makes final decisions regarding trial modifications. The committee ensured scientific rigor and ethical compliance through an independent review.

## Discussion

3

This cluster-randomized trial demonstrated the feasibility and potential impact of a pharmacist-led, multidimensional intervention aimed at reducing IV antimicrobial use in ED patients with bacterial URTIs. By integrating clinician education, evidence-based decision support, and patient education, the intervention aligns with global antimicrobial stewardship (AMS) priorities, while addressing context-specific challenges in China’s healthcare system.

To the best of our knowledge, this is the first study to investigate the impact of pharmacist-led interventions on decreasing irrational IV antimicrobial therapy in China. Pharmacist-led AMS programs have been effective in enhancing the appropriateness of antibiotic selection, timely administration, and reducing the duration of antimicrobial therapy. Elnour AA et al. reported that the clinical pharmacist’s implementation of the surgical antimicrobial prophylaxis protocol revealed a significant reduction in SSIs from 42.5% to 25.7% in the intervention group compared to the reduction from 57.5% to 44.2% the control group (*p* = 0.001) (24). Zhou et al. (25) revealed that the reasonable antibiotic rate increased significantly in terms of usage and dosage (96.6% versus 83.9%, *p* < 0.001), timing of administration (94.5% versus 78.4%, *p* < 0.001), and medication duration (64.4% versus 37.7%, *p* < 0.001) in patients undergoing orthopedic internal fixation during the pharmacist intervention period. This intervention framework, which targets prescriber behavior and patient perceptions, reflects the growing recognition that AMS success requires addressing the systemic and cultural drivers of antimicrobial misuse. The emphasis on IV-to-oral conversion criteria resonates with international guidelines advocating step-down therapies for stable infections. However, this approach uniquely adapts these principles to China’s high IV use setting. However, the 65% baseline IV antibiotic rate for pediatric URTIs reported in rural China underscores the entrenched prescribing norms that our intervention sought to disrupt (13). This study further demonstrated pharmacists’ unique capacity to translate national AMS policies into context-specific protocols. This adaptation of the IV-to-oral conversion criteria to accommodate China’s high patient volumes and diagnostic uncertainty exemplifies how pharmacists’ expertise can balance safety with feasibility. Nevertheless, sustainable impact requires institutionalizing pharmacists’ authority in antimicrobial decision-making, a cultural shift still underway in many Chinese hospitals.

The trial’s pragmatic design enhances real-world applicability, as evidenced by its integration into routine workflows, without requiring additional diagnostics. This scalability aligns with China’s 2025 National Medical Quality Goals, which prioritize feasible interventions to curb IV overuse. If the anticipated 12% relative reduction in IV antibiotic initiation is achieved, it could translate to substantial public health benefits, given China’s annual URTI burden. Extrapolating from this sample size assumption (n = 3,112), a 12% absolute reduction would eliminate approximately 1,200 unnecessary IV courses per 10,000 patients, mitigating associated adverse events, such as infusion reactions, AMR selection, and healthcare costs. Furthermore, the inclusion of patient education materials counteracts the pervasive misconceptions linking IV therapy to enhanced efficacy. This approach complements recent policy shifts toward value-based care by empowering patients to question unnecessary infusions.

This study has several limitations. First, it was not a double-blind study. Although efforts have been made to control bias, the telephone follow-up personnel and trial statisticians’ blinded design of this study could not avoid bias. Second, because this was a cluster-randomized trial, variations in baseline infusion rates across different hospitals may result in heterogeneity in outcomes. To minimize the impact of baseline infusion rate variation, we stratified randomization by hospital grade and baseline proportion of patients with URITs prescribed IV antibiotics. However, the exclusion of hospitals with baseline IV rates of < 50% limits the generalizability to low-performing settings. Third, the study period coincided with the nationwide implementation of AMS policies and increased awareness of IV antibiotic overuse, which may have introduced confounding factors. As such, it is difficult to disentangle the specific effect of our program from these concurrent secular trends. Finally, the 14-day follow-up window may underestimate late complications or AMR development, and long-term studies are needed to assess durability.

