### Trial design

2.2

This is a pragmatic, parallel-group, cluster-randomized controlled trial, stratified by hospital tier classification, comparing pharmaceutical interventions with usual care in 28 participating hospitals. This study was designed according to the Standard Protocol Items: Recommendations for Interventional Trials (SPIRIT) guidelines (2025). The flowchart of the study is presented in Figure 1. A cluster-randomized design was chosen because some aspects of the intervention made it infeasible to allocate doctors within the same hospital to different groups due to logistical reasons and potential contamination risks.

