#### Eligibility criteria for clusters

2.4.1

Hospitals were eligible to participate in the trial if they treated patients with URTI in the ED and had not previously implemented specific interventions to reduce the rate of IV antibiotic administration. Fifteen hospitals were excluded from the study due to significantly lower baseline rates of IV antibiotic use for URTIs than peer institutions, with rates consistently remaining at < 50%.

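### The Discussion claims stratification by baseline IV rate, the methods describe hospital grade alone, and the stated model has no baseline rate: the randomisation account needs correcting and available precision is forgone

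*Protocol article*

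**What the plan says.** The protocol article describes the stratification in three places.

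- Section 2.2 (Trial design): the trial is "stratified by hospital tier classification".
- Section 2.6 (Randomization): the 28 hospitals are counted by grade, "comprising 9 Tier-3 Grade-A hospitals, 15 Tier-3 Grade-B hospitals, and 4 Tier-2 Grade-A hospitals". Then: "All participating institutions were stratified by hospital grades to ensure balanced cluster distribution between the study arms", and "Hospitals within each stratum were randomly allocated to either the intervention or control group in a 1:1 ratio". Baseline infusion rate is not mentioned.
- Section 3 (Discussion, limitations): "we stratified randomization by hospital grade and baseline proportion of patients with URITs prescribed IV antibiotics". The stated purpose is to limit the effect of differing baseline infusion rates, which the same paragraph names as a source of heterogeneity.

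Section 2.11 (Statistical analysis) specifies generalized linear models "with treatment group, hospital level as fixed effects and healthcare center as a random effect". Hospital level is most naturally read as tier or grade. No baseline infusion rate appears.

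Two places indicate that baseline rates were measured. Section 2.4.1 reports that "Fifteen hospitals were excluded from the study due to significantly lower baseline rates of IV antibiotic use for URTIs than peer institutions", the rates in question being consistently below 50%. Section 2.4.2 defines eligible patients as those who "had a URTI diagnosis during the baseline and intervention periods".

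**The concern.** Sections 2.2 and 2.6 name one stratification factor and the Discussion names two. The Discussion relies on the second when it defends the trial against a limitation that it raises itself, so a reader judging how well the arms were balanced cannot tell which design was run.

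Each account leaves a gap:

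- **Baseline rate was a stratifier.** The model in section 2.11 leaves out a factor used in the randomisation.
- **Baseline rate was not a stratifier.** The safeguard claimed in the Discussion is absent. Baseline rate then enters only indirectly, through the exclusion of hospitals below 50% and whatever part of it follows hospital grade.

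With 28 hospitals and the planned ICC, most of the variance of the treatment comparison lies between hospitals. A hospital-level baseline measurement can reduce that component. At stake are the width of the confidence interval and, under the second account, protection against a chance difference in baseline prescribing between the arms.

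**Working it through.** **Inputs from section 2.5:** proportions 0.60 and 0.48; 14 hospitals per arm; 100 patients per hospital; ICC 0.04; two-sided 5% unpooled Z-test; stated power 82%.

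**Input not in the document:** r, the correlation between a hospital's baseline and trial-period IV rates beyond what grade explains. A range is used.

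**1. The plan's own figure.**
- Design effect = 1 + 99 × 0.04 = 4.96. Effective n per arm = 1400 / 4.96 = 282.3.
- SE = √[(0.60 × 0.40 + 0.48 × 0.52) / 282.3] = √(0.4896 / 282.3) = 0.0416.
- Power = Φ(0.12 / 0.0416 − 1.96) = 82.2%. The stated 82% reproduces.
- With a t reference on 24 df (28 hospitals less intercept, treatment and two grade terms), power is 78.9%.

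**2. Share of variance between hospitals.**
- Average p(1 − p) = 0.4896 / 2 = 0.2448.
- Between hospitals: 0.04 × 0.2448 = 0.00979. Within: 0.96 × 0.2448 / 100 = 0.00235.
- Share between hospitals = 0.00979 / 0.01214 = 81%.

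**3. Effect of adjusting for baseline rate.** SE = √{2 × [0.00979 × (1 − r²) + 0.00235] / 14}. The t reference has 23 df once the covariate is added.

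| Assumed r | SE | SE reduction | Power (Z) | Power (t) |
|---|---|---|---|---|
| unadjusted | 0.0416 | – | 82.2% | 78.9% (24 df) |
| 0.3 | 0.0401 | 4% | 84.9% | 81.7% (23 df) |
| 0.5 | 0.0372 | 11% | 89.7% | 87.0% (23 df) |
| 0.7 | 0.0324 | 22% | 96.0% | 94.4% (23 df) |

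The unadjusted row removes no variance for grade, although grade is in the model.

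**4. Sensitivity to the ICC.** Suppose hospital rates were uniform over 50–70%. Section 2.5 gives that range for the current infusion rate, but not as a distribution across hospitals, so this is an assumption.
- SD = 0.20 / √12 = 0.0577. Implied ICC = 0.0577² / 0.24 = 0.014.
- Between-hospital share is about 58%; unadjusted SE about 0.029; power about 98% (t, 24 df).
- Adjusting at r = 0.5 gives SE about 0.027 and power about 99%. The gain is small.

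**5. Chance imbalance if only grade was used** (ignoring balance gained through grade).
- ICC 0.04 at a rate of 0.60: between-hospital SD = √(0.04 × 0.24) = 9.8 points. SD of the arm difference in mean baseline rate = 9.8 × √(2/14) = 3.7 points; 95% range ±7.3.
- Uniform over 50–70%: 5.8 × √(2/14) = 2.2 points; 95% range ±4.3.
- The target difference is 12 points.

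**The case against.** The strongest defence has four parts.

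1. **The accounts may be compatible.** Neither section 2.2 nor section 2.6 says that grade was the only factor, and the Discussion repeats grade before adding baseline rate. The methods may simply be incomplete. This stands as far as it goes: a reader might infer that the safeguard is known to be absent, and the document does not support that. It does not remove the need for a correction, because section 2.6 sets out the hospitals by grade alone and the Discussion relies on the added factor.

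2. **The stated model is valid.** Under randomisation, treatment plus grade plus a random hospital effect gives a comparison that is unbiased in expectation, and leaving out a true stratifier is typically conservative. This stands in full. A reader might infer bias; the loss is only of precision and of protection against chance imbalance.

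3. **Baseline rate is not ignored.** The 50% cut restricts it, grade is both stratified and modelled, and the random effect carries the remaining hospital variation into the standard error. This also stands, so it would be wrong to say that nothing deals with baseline rate. Nor does the document show that it is the strongest available predictor, though it is a plausible one.

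4. **The analysis plan may add covariates.** Section 2.11 announces a detailed plan before data lock, and section 2.11.1 gives an imputation rule for baseline prognostic variables. This bears on the model, and it means that the covariate can still be prespecified. But section 2.11 already lists model terms, and how the hospitals were randomised is a matter of record that an analysis plan cannot decide.

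One caution concerns the data. Section 2.4.1 refers to rates for URTIs and does not say that they were measured in patients meeting the laboratory and prescribing criteria of section 2.4.2.

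**Conclusion.** The inconsistency is in the text and needs correcting. The missing baseline term is a missed opportunity and not an error that invalidates the analysis.

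Balance is lost only if sections 2.2 and 2.6 give the true account. If the Discussion is right, balance was addressed by design and the gap is an omitted design factor. A reader might infer that the sample size is wrong; it is not, since the stated 82% reproduces.

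At the planned ICC of 0.04, adjustment would reduce the standard error by about 4% to 22% for r between 0.3 and 0.7. These figures rest on an assumed r, which should be read as partial on grade. Excluding hospitals below 50% narrows the baseline range and may lower r, and a smaller ICC shrinks the gain further, as step 4 of the working shows. Confidence is high for the inconsistency and moderate at most for the size of the gain.

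**What to change.** - Take the stratification factor or factors from the randomisation record, state them in sections 2.2 and 2.6, and correct whichever section is wrong. If baseline rate was used, give its categories. If it was not, withdraw the claim in the Discussion.
- Before data lock, prespecify each hospital's baseline IV rate as a continuous fixed effect (for example on the logit scale) in the primary model beside hospital grade. Define the period and patients it is computed from, preferably matching the trial's eligibility criteria. Use a small-sample reference for the treatment test.
- Report baseline IV rate by arm.

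The cost is a text correction, one covariate that the sponsor appears to hold already, and one cluster-level degree of freedom (24 to 23). If the covariate explained nothing, power with a t reference would move only from 78.9% to 78.8%. The sample size does not change.
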